#### Secondary endpoints

Secondary endpoints will comprise:Other TCI prevention criteriaTime to first definitive or probable TCBSITime to first ESIIncidence rate of definitive or probable TCBSIIncidence rate of ESIPrevention of TC colonizations: rates of colonization of removed TCsCatheter patencyTime to first TC dysfunctionIncidence rate of TC dysfunctionsDialysis dose: monthly (Kt/V)_sp_ and (KT/V)_e_ (2nd generation Daugirdas equation) and Kt/V measured by the dialysis machine (ionic dialysance or optical measurement of urea in the effluent dialysate)TC survival: time to TC removalHealth care consumptionTime to first systemic antibiotic treatment for TCITotal duration and type of antibiotic treatmentTime to first hospitalization for TCITotal duration of hospital stays for TCITotal number of TCs replaced during the studySafetyIncidence rate of breaches in TC integrity (TC leakage or disruption)Incidence rate of clinical adverse events related to ethanol exposure (tiredness, ethanol taste, headaches, dizziness, nausea, light-headedness, and increase in serum aspartate aminotransferase, alanine aminotransferase, gamma-glutamyl transferase or alkaline phosphatase).Incidence rate of type II heparin-induced thrombocytopenia.Incidence rate of haemorrhages: bleeding or suspected bleeding, qualified as major if associated with a decrease in haemoglobin levels of more than 2 g/dL or the need to transfuse at least two units of red blood cells.Overall mortality: time to death from any causeInflammation: CRP value (measured every 3 months).

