### Design and setting of the study

ETERNITY is a prospective phase III multi-centre, single blind, randomized, controlled, parallel group study (Fig. 1). It will be carried out in 14 dialysis units in France (Additional file 2). The planned duration of the study will be 36 months. The enrolment period will be 24 months. Patients will receive the study treatment for up to 12 months or until 1 month before the end of the study. To evaluate safety, all the patients included will be followed for adverse events for 4 additional weeks after they have received their last treatment dose in the study (Fig. 2).

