### Endpoints

#### Primary endpoints

The primary outcome will be time to first TCI. In the study, TCI is a composite endpoint defined by the occurrence of at least one of the three following events: definitive TCBSI, probable TCBSI or ESI. TCI diagnosis and its type (definitive or probable TCBSI or ESI) will be assessed by an endpoint adjudication committee (EAC, see Additional file 1) blinded to study arm according to predefined criteria (Tables 1 and 2).

**Table 1 Tab1:** TC infections are defined according to the definitions of the guidelines of the DIALIN^6^ network

*TC exit-site infection*	
• Purulent discharge from the exit-site *Or* • Other local signs: redness or pain at the exit-site or along the subcutaneous tunnel (tunnellitis) *And at least one of the following criteria* - Fever (> 38.2 °C) *Or* - Positive blood culture drawn from one of the two lumens of the TC following aspiration of the lock *Or* - Polymorphonuclear leucocytosis In the absence of criterion for TC-related bloodstream infection

**Table 2 Tab2:** The definition of TCBSI is specified according to K/DOQI 2006 clinical practice guidelines for vascular access^57^ which distinguishes between definitive and probable TCBSI

*Definitive TC- related bloodstream infection*	*Probable TC-related bloodstream infection*

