#### Blinding

The recognisable smell of ethanol and the need to prepare the Ethenox lock solution makes it difficult to ensure the blinding of lock solutions by nurses despite the use of masks. The study will be performed single blind for the patients and the analysts.

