#### Study assessment

At each session, the nurse in charge of the patient will search for signs indicating the presence of a TCI or dysfunction using a check list (comprising clinical signs of infection and bacteriological samples, antibiotic treatment, TC lines inversion and fibrinolytic treatments) according to the usual practice of the dialysis centres and clinical practice guidelines [26, 28]. Data will be collected weekly in an electronic case report form specifically developed for the study. Data for adjudication of the primary outcomes and serious adverse events will be recorded continuously.

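### The ethanol tolerability endpoint is worded by cause, and only one arm receives ethanol; it should count the listed events in both arms whatever their judged cause

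*Protocol article*

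**What the plan says.** The safety part of Secondary endpoints lists the "Incidence rate of clinical adverse events related to ethanol exposure (tiredness, ethanol taste, headaches, dizziness, nausea, light-headedness", and closes the same item with "and increase in serum aspartate aminotransferase, alanine aminotransferase, gamma-glutamyl transferase or alkaline phosphatase". The other safety items there (loss of catheter integrity, type II heparin-induced thrombocytopenia, haemorrhage, death) are not tied to ethanol.

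Randomization assigns patients 1:1 to Ethenox or to UFH or citrate, according to the solution already in use.

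On who knows the allocation, Blinding says that the smell of ethanol and the need to prepare Ethenox "makes it difficult to ensure the blinding of lock solutions by nurses despite the use of masks". It then states: "The study will be performed single blind for the patients and the analysts". Under Primary endpoints, the diagnosis and type of TCI "will be assessed by an endpoint adjudication committee (EAC, see Additional file 1) blinded to study arm according to predefined criteria". No equivalent is stated for the ethanol events.

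On collection, Study assessment says that the nurse at each session "will search for signs indicating the presence of a TCI or dysfunction using a check list", described as "comprising clinical signs of infection and bacteriological samples, antibiotic treatment, TC lines inversion and fibrinolytic treatments". More generally, Design and setting of the study says that "all the patients included will be followed for adverse events for 4 additional weeks after they have received their last treatment dose". The data and safety monitoring committee reviews adverse events, with no restriction to those linked to ethanol.

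**The concern.** The endpoint is named by a cause that exists in one arm only. If an event must be linked to ethanol before it counts, nausea in a control patient has no route into the numerator, whereas the same nausea on Ethenox has one. Apart from ethanol taste, the listed symptoms are non-specific and could occur on any lock, and enzyme rises have many causes. Only a like-for-like count in the two arms separates an ethanol effect from background.

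The error can go either way. Staff who know the lock may link ordinary complaints to it and create an excess. They may also dismiss real intolerance as usual dialysis symptoms and hide one. Blinded analysts cannot undo a classification made before the data reach them.

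At stake is the trial's evidence on tolerance. The Background expects the lower ethanol concentration and the aspiration of the lock to improve it, and this endpoint bears most directly on that expectation. The primary outcome and the sample size are not affected.

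**Working it through.** **No stated figure to reproduce.** The article gives no event rate, power or sample size for this endpoint; the 400 patients and 90% power concern TCI. The check is therefore one of wording, followed by an illustration on assumed rates.

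**Two readings of the item**

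- *Literal:* an event counts only if linked to ethanol. The count then depends on how often events are linked in each arm.
- *Label:* the phrase explains why these events were chosen, and all of them are counted in both arms. Attribution plays no part.

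The list in brackets favours the label reading, because all its items except ethanol taste can readily be recorded in a UFH or citrate patient. The words before the bracket favour the literal one. The article does not settle it and names no assessor or causality step.

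**What the literal reading could do**

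From the article: 200 per arm (400 patients, 1:1) and a two-sided 5% level. Assumed: a true patient-level risk b, the same in both arms, and fractions a_E and a_C of events attributed to ethanol on Ethenox and on control. Patient proportions stand in for the article's incidence rates.

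Observed proportions: p_E = b × a_E and p_C = b × a_C. The apparent difference is b × (a_E − a_C), although the true difference is zero.

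Chance of a significant difference (normal approximation):

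Φ[(p_E − p_C − 1.96 × SE0) / SE1], where SE0 = √[2 p̄(1 − p̄)/200], p̄ is the mean of p_E and p_C, and SE1 = √{[p_E(1 − p_E) + p_C(1 − p_C)]/200}.

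Example with b = 10%, a_E = 50%, a_C = 25%:

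- p_E = 0.05, p_C = 0.025, p̄ = 0.0375
- SE0 = 0.0190, so 1.96 × SE0 = 0.0372; SE1 = 0.0190
- (0.025 − 0.0372)/0.0190 ≈ −0.645, and Φ(−0.645) ≈ 0.26

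With a_E = 50% throughout:

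| True risk, both arms | a_C = 0% | a_C = 10% | a_C = 25% | a_C = 50% |
|---|---|---|---|---|
| 10% | 90% | 65% | 26% | 5% |
| 20% | over 99% | 92% | 48% | 5% |
| 40% | about 100% | over 99% | 80% | 5% |

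The last column is equal attribution. Counting events whatever their cause (a_E = a_C = 100%) also gives 5%, at any background risk. The approximation is rough where the control count is zero.

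**The opposite direction.** Suppose the true risks are 40% on Ethenox and 30% on control. An all-cause count shows 40% against 30%. With no attribution on control, the literal count shows 0.40 × a_E against 0%. If staff attribute nothing, that is 0% against 0%, and a real 10-point excess is lost.

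**The case against.** The strongest reply is that the phrase is simply a heading for a prespecified list. On that reading nobody judges cause and there is no bias. This stands as a possible, perhaps the intended, reading. It does not remove the point, because the two readings can give very different results and the text does not choose between them.

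Second, a reader might infer that unblinded staff make the attribution and that the control arm therefore scores about zero by construction. The documents do not support this. No assessor or causality step is described, the zero follows only from the literal reading, and the enzyme rises are measurements available in either arm.

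Third, patients are blinded, and symptom reports would come from them. This is a real safeguard, though weakened because ethanol taste is itself on the list and the smell is acknowledged to be recognisable. It also protects reporting, not any later classification.

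Fourth, adverse events are followed in all patients and reviewed by an independent committee, so it would be wrong to say that ethanol harms are captured only through this endpoint. That stands, but it does not change how the endpoint is defined.

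Fifth, the session check list is described as a tool for infection and dysfunction, and an article may leave adverse-event collection to the full protocol. That stands too. The absence of these symptoms from the check list is not evidence that they go unsolicited, and no weight is placed on it here.

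Last, the rates in the illustration are all assumed. They show how sensitive the literal reading is, not what will happen in this trial.

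**Conclusion.** The point holds as a defect of wording in one secondary safety endpoint. The definition refers to a cause present in one arm, nurse blinding is conceded to be unreliable, and blinded adjudication is stated for TCI alone. Taken literally, this permits differential attribution of mostly non-specific events, which could create or conceal a difference.

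Its size in this trial is unknown. On assumed equal true risks of 10% to 40% and 50% attribution on Ethenox, the chance of a false difference runs from 26% (lowest risk, 25% attributed on control) to about 100% (highest risk, none attributed on control). It is 5% when attribution is equal or not required.

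A reader might go further and call the tolerability comparison invalid. The text does not show that: it is ambiguous, one of its readings is sound, and general adverse-event data are collected in both arms. This is a cheap improvement worth making.

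**What to change.** Reword the endpoint as the incidence, in both arms, of each listed symptom and each liver-enzyme rise, irrespective of judged cause. Ask about the symptoms in identical words in both arms; the existing per-session check list is one convenient place. Apply the same rule for an enzyme rise to every patient. Make the all-cause rates the comparison between arms, and report any attribution to ethanol descriptively only.

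The cost is a sentence in the endpoint definition and, if the check list is used, a few extra items. Treatment and sample size do not change. There are two drawbacks. More low-grade symptoms will be recorded in both arms, and nurses who know the lock may still influence what is written down, so the change removes bias from attribution but not all bias from recording.

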However, ethanol has no specific anticoagulant effect, and our group has previously reported an increase in the rates of TC dysfunction when a 60% *v*/v ethanol interdialytic lock solution is used [25]. Experimental data provide evidence that a mixture of ethanol and injectable anticoagulant may be a promising lock solution for preventing both TCI and TC dysfunctions. UFH, whatever its concentration, cannot be mixed in 40% v/v ethanol because of precipitation. ERA-EDTA recommends using low molecular weight heparins (LMWHs) for blood circuit anticoagulation during dialysis sessions. Like UFH, LMWHs have no antibiofilm properties. In contrast, they can be mixed in 40% v/v ethanol and among LMWHs enoxaparin has the highest solubility (up to 1300 U/mL). Our group has shown that 40% v/v ethanol - enoxaparin 400 U/mL is stable, compatible with TC materials and possesses antibiofilm and anticoagulant properties in vitro (patent). No clinical studies have previously assessed the efficacy of a combined solution of ethanol and LMWH in preventing TCI in chronic hemodialysis patients.

We assume that an interdialytic lock solution of Ethenox, a mixture of enoxaparin 1000 U/mL in 40% v/v ethanol, can be effectively and safely used to prevent TCI in chronic hemodialysis patients. The reduced concentration of ethanol in Ethenox compared to that in previous published reports and the aspiration of the lock before connection for dialysis will enhance tolerance while the addition of enoxaparin will effectively prevent the risk of TC dysfunction.

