### Description of the products

Ethenox solution is obtained by mixing a pre-packaged ethanol-saline solution with 0.6 mL of enoxaparin (10,000 U/mL) to achieve 6 mL of the required ethanol content and enoxaparin concentration (enoxaparin 1000 U/mL in 40% *v*/v ethanol). The pharmacy department of the university hospital of Clermont-Ferrand will prepare the ethanol-saline solution in flasks and will send them with enoxaparin syringes every 3 months.to the study centres in boxes containing 14 treatments.

UFH lock solution is pure sodium heparinate 5000 U/mL packaged in the form of a single-use ampoule, i.e. heparin 25,000 U / 5 mL. Citrate solution at 4% is packaged in the form of a single-use ampoule, i.e. sodium citrate 4% 5 mL.

Each centre is free to choose the antiseptic solution used but cannot change it during the course of the study. The use of an antiseptic ointment at the exit-site until wounds have healed or in the event of ESI is authorized in accordance with guidelines [26]. The use of a fibrinolytic lock solution is not allowed except in the event of TC dysfunction. The use of other antimicrobial locks is not allowed and nor is that of dressings impregnated with an antibiotic or antiseptic.

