#### Interim analysis and independent data and safety monitoring committee

An independent data and safety monitoring committee (Additional file 1) will analyse the adverse events, give its opinion on major amendments of the protocol, proceed to the interpretation of an intermediate analysis (at 1/3 of the inclusions) and if deemed necessary announce the suspension or early termination of the study.

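### Major haemorrhage is graded only by haemoglobin fall or transfusion need, so a fatal or critical-site bleed meeting neither could be classed as non-major

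*Protocol article*

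**What the plan says.** The Safety part of Secondary endpoints in the protocol article lists "Incidence rate of haemorrhages: bleeding or suspected bleeding". There is no severity threshold for entry, so any bleed, even a suspected one, is counted. The same item then sets the single severity grade: a haemorrhage is "qualified as major if associated with a decrease in haemoglobin levels of more than 2 g/dL or the need to transfuse at least two units" (red-cell units). The two criteria are alternatives, and no third is given.

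Other parts of the article bear on how bleeding is captured:

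- Secondary endpoints also lists overall mortality, as time to death from any cause.
- Study assessment states: "Data for adjudication of the primary outcomes and serious adverse events will be recorded continuously".
- The section on interim analysis and the data and safety monitoring committee says that the committee "will analyse the adverse events, give its opinion on major amendments of the protocol".
- Primary endpoints limits the described adjudication to infection: "TCI diagnosis and its type (definitive or probable TCBSI or ESI) will be assessed by an endpoint adjudication committee".
- The study lock is "a mixture of enoxaparin 1000 U/mL in 40% v/v ethanol". In the control arm, "UFH lock solution is pure sodium heparinate 5000 U/mL", with citrate 4% as the alternative according to the solution used before inclusion.

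**The concern.** Both criteria measure the volume of blood lost. Volume is a reasonable marker of severity for many bleeds, but a poor one where the harm comes from the site. An intracranial or pericardial bleed can disable or kill with little fall in haemoglobin and no transfusion. A site that applies the sentence as written would record such a bleed as a haemorrhage but not as a major one.

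The major category is the only severity grade in this endpoint. Because entry is so broad, the ungraded remainder runs from a suspected ooze at the exit site upwards. A low-volume critical-site bleed would be tabulated with those events. A reader of the final bleeding table would then see a major-bleed count that could omit some of the clinically worst events, in a trial where enoxaparin is part of the study lock and a heparin lock is one of the two control options.

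**Working it through.** No arithmetic applies. The article states no bleeding rate and no target for this endpoint, so there is no figure to reproduce. The check is to read the definition as a rule and apply it to cases.

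**The rule**

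Major = bleed AND (haemoglobin fall > 2 g/dL OR need for at least 2 red-cell units).

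**Applied to cases** (chosen for illustration, not taken from the article)

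| Case | Counted as haemorrhage | Graded major |
|---|---|---|
| Minor exit-site ooze, haemoglobin stable | yes | no |
| Any bleed with a haemoglobin fall above 2 g/dL | yes | yes |
| Any bleed needing two or more units, fatal or not | yes | yes |
| Death from massive blood loss before a repeat haemoglobin or any transfusion | yes | yes if need is judged to have existed; no if the site looks only for units given |
| Low-volume intracranial bleed, patient survives | yes | no |
| Low-volume intracranial bleed, patient dies | yes | no |
| Symptomatic pericardial bleed with little volume loss | yes | no |

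The first row and the last three rows receive the same grade. The gap is conditional: a fatal or intracranial bleed that meets either criterion is graded correctly. Low-volume critical-site bleeds clearly fall outside the rule. Rapid death from blood loss depends on how a site reads the word need.

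**Does other text in the article close the gap?**

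1. *Overall haemorrhage rate.* It keeps the event but carries no severity information.
2. *All-cause mortality.* It captures the death but does not attribute it to bleeding, and it does not capture survivors of a critical-site bleed.
3. *Serious adverse events.* On the assumption that the trial's seriousness criteria are the customary ones, a fatal or intracranial bleed would be recorded here. That preserves the case record but does not change its class in the bleeding endpoint.
4. *Adjudication.* The committee's described task is the diagnosis and type of catheter infection. No review of bleeding is described that would regrade an event classed literally at the site.

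None of the four adds a fatal or critical-site criterion to the major grade. The events are captured, but the grade is incomplete.

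**The case against.** The strongest case against is that no event disappears. The named endpoint is the rate of all haemorrhages, and major is only a qualifier inside it. Deaths and serious adverse events are collected separately. The transfusion criterion refers to need, not to units given, so many deaths from blood loss already qualify. The same rule applies to both arms. The source is a one-line entry in a journal article that condenses a fuller protocol, where a wider grading may exist. All of this stands, and it makes the point small. It does not remove it: the published sentence reads as a complete rule, and that rule leaves out low-volume critical-site bleeds.

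A reader might infer more than the article supports, in four ways:

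- *That every fatal or intracranial bleed would be graded non-major.* It would not. Those that meet either criterion are major.
- *That the safety comparison could be reversed, or that a given share of major bleeds would be missed.* With no bleeding rate in the article, any percentage would only restate its own assumptions. Nor does the article give grounds for expecting the missed events to fall in one arm. Where unfractionated heparin is the local practice, the control lock is an anticoagulant too.
- *That the monitoring committee would be misled.* The article says that the committee analyses adverse events. It does not tie that review, or any stopping decision, to the major grade.
- *That the Background's remark on the absence of earlier clinical studies of an ethanol and low molecular weight heparin lock makes the case stronger.* That remark concerns efficacy and says nothing about bleeding or its classification.

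**Conclusion.** The point holds in a limited form. As published, the definition could class as non-major a fatal or critical-site bleed that meets neither the haemoglobin nor the transfusion criterion. The consequence is confined to the only severity grade within one secondary safety endpoint. Event capture, the primary endpoint and the sample size are not affected.

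The frequency of such misgrading cannot be estimated from the article, and no direction of bias between the arms is claimed. The conclusion rests on two assumptions: that sites would apply the published sentence literally, and that the full protocol or analysis plan, which is not shown, does not already contain a wider definition. It is a minor improvement worth making because it is cheap and uncontroversial.

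**What to change.** Keep both existing criteria and extend the definition of major haemorrhage with a third: any fatal bleed, or any symptomatic bleed in a critical site. The sponsor should list the critical sites in advance (for example intracranial and pericardial), since the article contains no such list. Use the extended definition in the safety tables for both arms. The fatal-bleed criterion also settles how to grade a patient who dies before a repeat haemoglobin or transfusion. Death and bleeding site are objective facts, which suits a trial in which the article accepts that nurses are hard to blind.

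If the full protocol already has such a definition, the sponsor need only confirm it and align the published text.

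The cost is one sentence in the endpoint definition, one case-report-form item, and a slightly higher count of major bleeds. No treatment, sample size or primary analysis changes.
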